## Abstract

**Background:**

Postoperative pain management plays a crucial role in determining the quality of recovery following thoracic surgery. However, achieving high-quality postoperative analgesia that facilitates satisfactory recovery remains challenging due to suboptimal pain control and side effects associated with conventional analgesic strategies. This study aims to evaluate the effect of single-injection thoracic paravertebral block with liposomal bupivacaine on the overall quality of recovery in patients undergoing thoracic surgery.

**Methods:**

This single-center, open-label, randomized controlled trial will enroll 162 patients scheduled for video-assisted thoracic surgery. Participants will be randomly allocated in a 1:1:1 ratio to three groups (*n* = 54 each): Group L will receive ultrasound-guided thoracic paravertebral block with liposomal bupivacaine; Group R will receive ropivacaine-based paravertebral block combined with opioid-based patient-controlled intravenous analgesia; and Group P will receive opioid-based patient-controlled intravenous analgesia alone. The primary outcome is the quality of recovery assessed by patient-reported Quality of Recovery-15 scores on postoperative days 1–3. Between-group differences will be analyzed using generalized estimating equations. Secondary outcomes include: pain-free interval; resting and cough-induced pain intensity at 6, 12, 24, 48, and 72 h; worst pain scores at 24, 48, and 72 h; perioperative opioid use; time to first rescue analgesia and times of request; patient confidence in coughing and ambulation; anxiety and sleep quality at 24, 48, and 72 h; patient satisfaction; postoperative nausea and vomiting incidence/severity and rescue antiemetic use. Safety outcomes comprise block-related complications and postoperative complications. All adverse events will be documented throughout the study.

**Discussion:**

This study aims to provide high-quality evidence on the efficacy of a single-injection thoracic paravertebral block with liposomal bupivacaine for post-thoracic surgery analgesia, compared with opioid-based intravenous analgesia alone and the combination of ropivacaine paravertebral block with systemic opioid analgesia.

**Clinical trial registration:**

Identifier: ChiCTR2500107787.

## Introduction

1

Although contemporary thoracic surgery is performed with video-assisted thoracoscopic surgery (VATS), which offers a minimally invasive approach, patients who undergo such procedures still experience moderate to severe postoperative pain, that can be attributed to rib retraction, intercostal nerve injury, and the irritation of the pleura by drainage tubes (1–4). This discomfort may negatively impact both postoperative recovery and quality of life (5). Efficient cough and expectoration is integral to the mitigation of pulmonary infection rates, and the commencement of early and vigorous ambulation is instrumental in reducing the incidence of lower extremity deep vein thrombosis (1, 6, 7), however, these necessary postoperative recoveries are often accompanied by an exacerbation of pain. Therefore, optimal postoperative pain management is crucial for enhancing the quality of patient recovery.

Postoperative pain management employs various approaches—including epidural, intravenous, regional, and local analgesia—with differing efficacy levels. In Canada, epidural analgesia remains preferred for open thoracic surgery, while 41% of clinicians use it for thoracoscopic procedures and 27% favor intravenous analgesia (8). Catheters and opioids, despite limitations, are indispensable in Enhanced Recovery After Surgery (ERAS)-aligned pain management (9–11). Catheter-based techniques carry risks of occlusion, dislodgement, and infection. Although established in practice, epidural analgesia may cause unavoidable discomfort, neurological injury, hematoma, hypotension, urinary retention, and cardiovascular complications (8, 12–14). Intravenous analgesia usually relies on opioids, which frequently cause postoperative nausea and vomiting (15, 16). Therefore, an ideal postoperative pain management strategy should eliminate both catheters and opioids.

Prospect guidelines for video-assisted thoracoscopic surgery explicitly advocate for the use of thoracic paravertebral nerve block (PVB) as the preferred modality for postoperative pain management following thoracoscopic surgery (7). Studies have shown that thoracic PVB is comparable to epidural analgesia in terms of pain relief efficacy (1, 17–19). However, effective postoperative analgesia requires both sufficient intensity and duration. Single-injection nerve blocks are limited by the short duration of conventional local anesthetics. Liposomal bupivacaine represents a novel extended-release local anesthetic formulation with an established safety profile. Utilizing multivesicular liposome technology, the agent encapsulates bupivacaine within phospholipid vesicles (20). This structural design facilitates progressive drug release, maintaining stable plasma concentrations and thereby enabling prolonged, high-quality analgesia. Its distinct pharmacokinetic profile supports its potential in postoperative pain management, making single-injection regional anesthesia a feasible standalone analgesic strategy.

This study will evaluate a novel analgesic strategy combining paravertebral block with liposomal bupivacaine in thoracic surgery. The approach is expected to provide analgesic efficacy comparable to that of continuous catheter-based techniques while substantially reducing complication rates, thereby enhancing postoperative recovery quality. These findings will provide crucial evidence supporting the implementation of catheter-free and opioid-free pain management protocols in postoperative care.

## Methods

2

This protocol adheres to the Standard Protocol Items: Recommendations for Interventional Trials (SPIRIT) guidelines.

### Study design and patients

2.1

This study is a single-center, prospective, randomized, open-label, parallel-group clinical trial. The trial will be conducted at the Affiliated Hospital of Qingdao University, enrolling a total of 162 patients. Recruitment is scheduled to take place from 18th August 2025 to 7th May 2026. The study flow diagram is shown in Figure 1.

**Figure 1 fig1:**
[figure not shown]
Study flow diagram.

### Inclusion criteria

2.2

Eligible participants will be adults aged 18 to 90 years scheduled for unilateral thoracoscopic surgery, with an American Society of Anesthesiologists (ASA) physical status of I to III, who provide written informed consent.

### Exclusion criteria

2.3

Exclusion criteria will include:

Known allergy to local anesthetics, nonsteroidal anti-inflammatory drugs, or opioids;Preexisting chronic pain of thoracic or back origin;Contraindications to regional puncture such as coagulopathy, local infection or inflammation;Psychiatric disorders;History of ipsilateral thoracotomy;Referral for thoracotomy;History of chronic opioid use or substance abuse;Bilateral surgery.

### Primary outcome

2.4

The primary outcome of this study is the composite score of the Quality of Recovery-15 (QoR-15) score at 24, 48, 72 h postoperatively. The QoR-15 is a multidimensional patient-reported instrument designed to evaluate functional recovery after surgery. It comprises five domains: physical comfort (5 items), physical independence (2 items), pain (2 items), emotional state (4 items), and psychological support (2 items). Each item is rated on a 10-point scale, ranging from 0 (never) to 10 (all of the time) (scores for negative items are reversed). Higher QoR-15 scores indicate better quality of recovery after surgery.

### Secondary outcomes

2.5

Secondary outcomes will include the pain-free interval (defined as the time from the end of surgery to the first onset of pain), resting and cough-evoked pain Visual Analog Scale (VAS) scores (ranging from 0, no pain, to 10, worst imaginable pain) assessed at 6, 12, 24, 48, and 72 h postoperatively; maximum pain scores at 24, 48, and 72 h; intraoperative and total postoperative opioid consumption; time from the end of surgery to first request for rescue analgesia and the number of such requests; anxiety and sleep quality (using numeric rating scores, NRS, 0–10, higher indicating greater anxiety/ greater sleep) at 24, 48, and 72 h; patient satisfaction with analgesia measured using an NRS (0–10, higher indicating greater satisfaction); incidence and severity of postoperative nausea and vomiting (PONV), graded on a 4-point scale (0 = none, 1 = nausea only, 2 = 1–3 vomiting episodes, 3 = ≥4 episodes) and the number of rescue antiemetic administrations at 24, 48, and 72 h; as well as patient confidence in coughing and ambulation, both assessed using an NRS (0 = no confidence to 10 = full confidence). All postoperative assessments will be performed daily at 17:00 until 3 days after surgery. The following outcomes will be recorded prior to patient discharge: the incidence of pneumothorax or hemothorax during the entire postoperative period, total postoperative drainage volume, and length of hospital stay.

### Safety outcomes

2.6

Safety outcomes will include the adverse events related to regional nerve blockade, such as allergic reactions, total spinal anesthesia, severe hypotension, malignant arrhythmias, and cardiac arrest, as well as postoperative complications including urinary retention, puncture site infection, pulmonary infection, deep vein thrombosis, pulmonary embolism, and atelectasis. All adverse events will be recorded and assessed throughout the study period.

### Randomization and blinding

2.7

This open-label, three-arm randomized trial will assign 162 participants in a 1:1:1 ratio (Group L, Group R, and Group P, with 54 participants per group). An open-label design will be adopted due to fundamental differences in postoperative pain management protocols among the three groups. To facilitate protocol-adherent adjustments in analgesia, both investigators and participants will not be blinded to treatment allocation. Nevertheless, postoperative outcome assessments will be performed by trained nurses who are not involved in the intervention procedures to minimize potential bias.

### Anesthetic and study interventions

2.8

All patients will fast for at least 8 h and refrain from clear fluids for at least 4 h prior to surgery. In the operating room, following the establishment of peripheral intravenous access, patients will receive oxygen via face mask at 5 L/min and undergo continuous monitoring of vital signs, including non-invasive blood pressure, percutaneous arterial oxygen saturation (SpO₂), heart rate, respiratory rate, and bispectral index (BIS). Under aseptic conditions, a radial arterial catheter will be inserted for continuous invasive arterial pressure monitoring. Anesthesia induction will be performed using propofol (2 mg/kg), sufentanil (0.5 μg/kg), and rocuronium (0.6 mg/kg). After induction of anesthesia, adequate topical anesthesia of the larynx and upper trachea will be achieved using lidocaine. Following preoxygenation, a double-lumen endobronchial tube will be placed. Correct positioning and depth of the double-lumen tube will be confirmed before initiating mechanical ventilation. The patient will then be repositioned into the lateral decubitus position with the surgical side uppermost.

A single senior anesthesiologist will perform ultrasound-guided thoracic paravertebral blocks under sterile conditions for all patients in groups L and R. The target injection levels are T4 and T6. For group L, under real-time ultrasound guidance and after confirming correct needle tip position, 10 mL of liposomal bupivacaine (133 mg/20 mL) (21) will be injected at each of the T4 and T6 levels according to a standardized technique, for a total volume of 20 mL. For group R, under identical ultrasound-guided and aseptic conditions, 10 mL of ropivacaine (0.5%) will be injected at each of the T4 and T6 levels, for a total of 20 mL. Patients in group P will not receive any nerve block. Following surgery, patient-controlled intravenous analgesia (PCIA) will be prepared for patients in groups R and P, but not for those in group L. Each PCIA pump will be prepared with a total volume of 100 mL, containing sufentanil and 8 mg of ondansetron. The total sufentanil dose will be calculated as 2 μg per kilogram of body weight. The background infusion will be set at a rate of 0.04 μg/kg/h. Additionally, the PCIA protocol will be configured with a bolus dose of 0.04 μg/kg and a lockout interval of 15 min to ensure medication safety.

An emergency response team will be established in this study to promptly manage patients with breakthrough severe pain and nausea/vomiting, ensuring rapid symptom relief. The acute pain management protocol will include acetaminophen and oxycodone: initially, 1 g of intravenous acetaminophen will be administered every 6 h (maximum daily dose not exceeding 4 g). If the patient experiences intolerable pain (Visual Analog Scale score > 4) for more than 30 min, or if the maximum daily dose of acetaminophen has been reached, oral oxycodone 5 mg will be administered instead, with dose adjustments within the safe range as needed. Subsequent doses may be repeated every 4 to 6 h under close monitoring and strict control of dosage variations. For participants in groups R and P using PCIA, rescue analgesia will be implemented according to a tiered protocol. If intolerable pain occurs despite the preset continuous sufentanil background infusion, PCIA bolus doses will be administered as the first-line rescue strategy. Should pain remain uncontrolled after reaching the maximum allowable bolus dose, the subsequent, predefined rescue analgesic protocol will then be initiated. For acute episodes of severe nausea and vomiting, potential underlying causes will first be assessed to exclude gastrointestinal symptoms resulting from other primary conditions. Once other causes are ruled out, ondansetron 4 mg will be administered intravenously as rescue therapy (maximum daily dose not exceeding 16 mg). Dosage adjustments may be made based on symptom severity within established safety limits.

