Study interventions									
Liposomal bupivacaine			×						
Ropivacaine & PCIA			×						
PCIA			×						
Outcome assessment									
QoR-15						×	×	×	
Pain-free interval				×	×	×	×	×	
VAS for pain at rest				×	×	×	×	×	
VAS for pain during cough				×	×	×	×	×	
Maximum VAS for pain						×	×	×	
First rescue analgesia				×	×	×	×	×	
Times of rescue analgesia				×	×	×	×	×	
Opioid consumption			×						×
NRS for anxiety						×	×	×	
NRS for sleep quality						×	×	×	
Analgesic Satisfaction									×
Incidence of PONV						×	×	×	
Severity of PONV						×	×	×	
Times of rescue antiemetic						×	×	×	
Confidence in coughing						×	×	×	
Confidence in ambulation						×	×	×	
Pneumothorax									×
Hemothorax									×
Drainage volume									×
Length of hospital stay									×
Adverse events									
Allergic			×	×	×	×	×	×	×
Total spinal anesthesia			×	×	×	×	×	×	×
Hypotension			×	×	×	×	×	×	×
Malignant arrhythmias			×	×	×	×	×	×	×
Cardiac arrest			×	×	×	×	×	×	×
Urinary retention			×	×	×	×	×	×	×
Puncture site infection			×	×	×	×	×	×	×
Pulmonary infection			×	×	×	×	×	×	××
Deep vein thrombosis			×	×	×	×	×	×	×
Pulmonary embolism			×	×	×	×	×	×	×
Atelectasis			×	×	×	×	×	×	×

According to SPIRIT, statement of defining standard protocol items for clinical trials.

Pre-op, preoperative; Intra-op, intraoperative; Post-op, postoperative; QoR-15, quality of recovery-15 scale; VAS, visual analogue scale; NRS, numerical rating scale; PCIA, patient-controlled intravenous analgesia pump; PONV, postoperative nausea and vomiting.

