### Statistical analysis

2.11

The normality of continuous variables will be assessed using the Shapiro–Wilk test. Data following a normal distribution will be reported as mean (standard deviation, SD), while non-normally distributed data will be presented as median (interquartile range, IQR). Binomial variables will be expressed as proportions. The correlation structure will be selected based on the quasi-likelihood under the independence model criterion (QIC). Data distribution will determine the use of either a normal or gamma distribution with identity or log-link functions. The primary hypothesis of this study is that group L can demonstrate a superior quality of postoperative recovery compared to both control groups, with the difference being both statistically and clinically significant. A generalized estimating equation (GEE) model will be used to analyze repeated measures of continuous variables accounting for within-subject correlations. Continuous variables measured at a single time point will be analyzed using *t*-tests or Mann–Whitney U tests depending on normality and categorical data will be analyzed using the χ^2^ test. Post-hoc pairwise comparisons are strictly contingent on a significant overall between-group difference and *p*-values are adjusted using the Bonferroni method and set at 0.017. For longitudinal outcomes, this correction governs testing at both the individual time-point and overall treatment effect levels, ensuring robust control of the type I error rate. Statistical significance will be defined as *p* < 0.05.

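### Postoperative opioid use is read only at discharge, by when any uninterrupted sufentanil pump has delivered the same 2 μg/kg in group R and group P, so early differences in demand cannot show in the pump part

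*Protocol article*

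**What the plan says.** Section 2.8 (Anesthetic and study interventions) gives groups R and P an identical patient-controlled pump after surgery; group L has none. On the fill it states "The total sufentanil dose will be calculated as 2 μg per kilogram of body weight". On the basal rate it states "The background infusion will be set at a rate of" 0.04 μg/kg/h. The bolus is 0.04 μg/kg with a 15 min lockout. The article mentions no refill and no stop time.

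The same section sets the rescue order for R and P: "PCIA bolus doses will be administered as the first-line rescue strategy". Acetaminophen and then oral oxycodone follow only when boluses have been exhausted.

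Section 2.5 (Secondary outcomes) lists "intraoperative and total postoperative opioid consumption" and, separately, "time from the end of surgery to first request for rescue analgesia and the number of such requests". The Discussion describes the first of these as sufentanil over the operation and the hospital stay.

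In Table 1 (Section 2.9) the row "Opioid consumption" is marked only in the intraoperative and discharge columns. The row "Times of rescue analgesia" is marked at 6, 12, 24, 48 and 72 h.

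**The concern.** Two choices that the article fixes work against each other. The pump holds a set dose per kilogram with a background rate that uses it up in about two days. The only postoperative reading of opioid use comes after that. Once the reservoir is empty, a patient who pressed the button often and one who never pressed it have the same pump total.

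This matters most for R versus P, because that contrast adds a ropivacaine block to the same pump. The Discussion cites earlier work in which paravertebral block lowered opioid use compared with opioid PCIA. If the ropivacaine block lowers demand in the first day, one would look for it here. A result of no difference could come from the fixed reservoir and be read as no effect of the block on opioid demand.

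**Working it through.** The plan gives no figure for pump run time or expected consumption, so there is nothing of its own to reproduce. The check is direct arithmetic on the settings in Section 2.8.

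Inputs:
- pump content 2 μg/kg
- background 0.04 μg/kg/h
- bolus 0.04 μg/kg, lockout 15 min, so at most 4 boluses per hour
- reading time: discharge, placed after the 72 h column in Table 1

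**Time to empty.** With b boluses in total, time to empty = (2 − 0.04b)/0.04 = 50 − b hours. With no boluses this is 50 h, with 10 it is 40 h and with 20 it is 30 h. With a bolus at every lockout the rate is 0.04 + 4 × 0.04 = 0.20 μg/kg/h, and the pump is empty at 2/0.20 = 10 h.

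**Dose delivered by hour t with b boluses so far.** D(t, b) = min(2, 0.04t + 0.04b) μg/kg. From 10 h on, the lowest possible value is 0.04t and the highest is 2, so the possible spread between patients is 2 − 0.04t until it reaches zero.

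| Reading or stop time | Lowest (μg/kg) | Highest (μg/kg) | Spread (μg/kg) | Boluses needed to reach 2 μg/kg |
|---|---|---|---|---|
| 24 h | 0.96 | 2.00 | 1.04 | 26 |
| 36 h | 1.44 | 2.00 | 0.56 | 14 |
| 40 h | 1.60 | 2.00 | 0.40 | 10 |
| 44 h | 1.76 | 2.00 | 0.24 | 6 |
| 48 h | 1.92 | 2.00 | 0.08 | 2 |
| 50 h and later | 2.00 | 2.00 | 0 | 0 |

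At an assumed 70 kg, the 48 h spread is 0.08 × 70 = 5.6 μg. Expressed in μg, the total of an emptied pump is simply 2 × body weight, so its variation between patients reflects weight and not analgesic need.

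**Illustration** (assumed: 5 boluses in one patient and 10 in another, all within 24 h):
- at 24 h: 1.16 versus 1.36, difference 0.20 μg/kg
- at 40 h: 1.80 versus 2.00, difference 0.20
- at 44 h: 1.96 versus 2.00, difference 0.04
- from 45 h: 2.00 versus 2.00, difference 0

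A difference that is fully visible at 24 h has gone before the 48 h visit, and well before discharge.

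**What can still differ at discharge.** Oxycodone rescue, pumps stopped early, and the intraoperative opioid. Under the rescue order in Section 2.8, extra need is drawn first from the fixed reservoir and then met with acetaminophen, so only need beyond both reaches oxycodone. On the Discussion's sufentanil-only description, oxycodone would not be counted at all; Section 2.5's wording covers all opioids.

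**The case against.** The strongest reply is that the outcome measures what it names. A cumulative total is naturally entered once, at close-out, and if both groups receive the full 2 μg/kg then their pump consumption really is equal. This stands. A reader might infer that the discharge total conceals an opioid saving made by the block. The documents do not support that: over the whole stay no pump opioid was saved, and what is lost is information on early demand.

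A second reply is that early need is recorded elsewhere. Boluses are the first rescue tier, the bolus size is fixed, and rescue requests are scheduled at 6 to 72 h, as are pain scores. This stands in part. If boluses count as requests, the counts track bolus use while the pump runs. The article does not say whether they do, and a count is not an opioid dose.

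A third reply is that pumps may be stopped early and that refill, stop and bolus-counting rules may sit in the full protocol. This is fair, and their absence from an article is not held against the plan. It limits the point to pumps run without interruption. It does not remove the ceiling, which follows from the stated settings and the stated reading time. Where stop times vary, the total also mixes run time with need.

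Finally, Section 2.11 states the hypothesis as "group L can demonstrate a superior quality of postoperative recovery compared to both control groups", so R versus P is not the main question. That also stands, and it keeps the point minor.

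**Conclusion.** The point holds as a minor design weakness. For any R or P pump run without interruption, the pump part of the postoperative total is exactly 2 μg/kg from 50 h on, so the R-versus-P difference in that part is zero per kg by construction.

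It rests on three assumptions: no refill, no early stop, and discharge after 50 h. The article states no refill or stop rule, and Table 1 places discharge after 72 h. The point holds almost fully for pumps stopped at 48 h or later (spread at most 0.08 μg/kg) and weakens if many are stopped by about 40 h (spread 0.40 μg/kg). The article gives no such share.

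A reader might go further and conclude that the opioid outcome is uninformative, or that the trial's main comparisons suffer. Neither follows. Oxycodone, early stops and intraoperative opioid can still separate R from P. Group L has no pump, so its opioid comparisons keep their meaning. QoR-15 does not depend on the pump reading.

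**What to change.** At the existing 24 h visit, read the delivered pump sufentanil and the bolus count from the pump. Repeat at 48 h for description only, since little spread is left by then. Record the time each pump is stopped or found empty.

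Report 0–24 h opioid consumption for R versus P, as pump sufentanil plus oxycodone in one stated equivalent, beside the total to discharge. Keep Section 2.5's all-opioid definition for both. If the full protocol does not already do so, say whether a pump bolus counts as a rescue request.

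The cost is a few case report form fields, a pump reading at two existing visits, and one more secondary analysis under the plan's multiplicity rule. The conversion factor between sufentanil and oxycodone is an assumption and must be stated. Treatment and sample size do not change.

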## Discussion

3

This prospective, open-label, randomized controlled trial plans to enroll 162 adult patients at our center. It is designed to evaluate the effect of a single ultrasound-guided paravertebral block using liposomal bupivacaine on postoperative recovery quality compared to conventional opioid-dependent intravenous analgesia and an established high-quality multimodal analgesia protocol. The trial will be conducted in accordance with the Consolidated Standards of Reporting Trials (CONSORT) guidelines. In addition to assessing overall recovery quality, the study will address three key clinical questions: whether the intervention provides sufficient baseline analgesia; whether it independently meets current standards for comprehensive pain management; and whether it confers significant clinical benefits beyond analgesia. The primary outcome is the overall quality of recovery, as measured by QoR-15 score at 24, 48, and 72 h after surgery. Secondary outcomes include multiple pain management quality assessments (such as pain-free interval and pain scores under various conditions), total consumption of sufentanil during surgery and hospitalization, anxiety and sleep quality scores at 24, 48, and 72 h postoperatively, the incidence and severity of PONV along with the use of rescue antiemetics at the same intervals, and patient confidence in coughing and ambulation assessed using an NRS. All postoperative evaluations will be performed daily at 17:00 until 3 days after surgery. Additional recorded outcomes include the incidence of pneumothorax or hemothorax, total postoperative drainage volume, and length of hospital stay.

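### The rescue endpoints count different events in group L than in groups R and P, and the opioid outcome is all opioids in the Methods but sufentanil only in the Discussion

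*Protocol article*

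**What the plan says.** **Rescue endpoints.** Section 2.5 lists, for all arms alike, "time from the end of surgery to first request for rescue analgesia and the number of such requests". Table 1 schedules first rescue and times of rescue without distinguishing arms.

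**Rescue pathway.** Section 2.8 states that "patient-controlled intravenous analgesia (PCIA) will be prepared for patients in groups R and P, but not for those in group L". The general rescue route is set out as "The acute pain management protocol will include acetaminophen and oxycodone". For R and P the same section adds a step before it: "PCIA bolus doses will be administered as the first-line rescue strategy". It continues: "Should pain remain uncontrolled after reaching the maximum allowable bolus dose, the subsequent, predefined rescue analgesic protocol will then be initiated". L has no such step.

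**Opioid endpoint.** Section 2.5 names "intraoperative and total postoperative opioid consumption". The abstract and Table 1 also speak of opioids in general. The Discussion, recapitulating the secondary outcomes, instead gives "total consumption of sufentanil during surgery and hospitalization".

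**The concern.** The rescue endpoints are meant to compare how soon and how often analgesia failed to hold. Under the plan's own label, the first rescue event in R and P is a press of a pump button that L patients do not have. In L it is a drug given under the acute pain protocol. The same endpoint name therefore covers different events, and the article does not say whether a bolus is a counted request. R and P share the pump, so the problem concerns L versus R and L versus P, not R versus P.

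The opioid outcome has a related problem. L's only protocol-specified opioid after surgery is oral oxycodone, which a sufentanil total leaves out.

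These outcomes bear on the trial's catheter-free and opioid-free rationale. The Discussion says the secondary outcomes will be used to assess analgesic quality and the clinical significance of the opioid-sparing approach. Section 2.11 extends multiplicity correction to secondary outcomes where applicable, so they are evidently to be tested. A difference produced by the counting rule could then be reported as an effect of the block.

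**Working it through.** The article states no figure for these endpoints that could be reproduced. The check sets the passages side by side and does arithmetic on the pump and rescue settings.

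**Inputs (all from section 2.8).**
- Pump: R and P yes, L no.
- Pump content: "The total sufentanil dose will be calculated as 2 μg per kilogram of body weight".
- Background infusion: 0.04 μg/kg/h.
- Bolus 0.04 μg/kg, lockout 15 min.
- Sufentanil at induction, every arm: 0.5 μg/kg.
- Acetaminophen every 6 h; oxycodone repeatable every 4 to 6 h.

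**Step 1: the two readings of a rescue request.**

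| Reading | First counted event in R and P | First counted event in L | Direction |
|---|---|---|---|
| Boluses count | Pump bolus | Acetaminophen or oxycodone | R and P tend to look earlier and more frequent; favours L |
| Boluses do not count | Acetaminophen or oxycodone, after the bolus maximum | Acetaminophen or oxycodone | R and P delayed; against L |

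The two readings push the comparison in opposite directions, and neither puts the arms on one scale.

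**Step 2: how many boluses are possible.** The lockout allows 60/15 = 4 per hour, but the reservoir limits how long that can last. Assuming one pump fill:
- At the full rate the pump uses 0.04 + 4 × 0.04 = 0.20 μg/kg/h. It empties in 2/0.20 = 10 h, after 40 boluses.
- Spread over the first 24 h, with the background running, the limit is (2 − 0.96)/0.04 = 26 boluses.

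In L, the dosing intervals allow 24/6 = 4 acetaminophen doses and 24/6 to 24/4 = 4 to 6 oxycodone doses a day. These limit doses. The endpoint counts requests, which a dosing interval does not cap, so the figures show that the units differ but do not predict a ratio.

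**Step 3: a sufentanil-only total.** Background infusion alone gives R and P:
- by 24 h: 0.04 × 24 = 0.96 μg/kg
- by 48 h: 0.04 × 48 = 1.92 μg/kg
- reservoir empty with no bolus at all: 2/0.04 = 50 h

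L's postoperative sufentanil under the protocol is 0 μg/kg, however much oxycodone is given. Adding the induction dose, the protocol-specified sufentanil by 24 h (before any bolus) is 0.5 μg/kg in L and 0.5 + 0.96 = 1.46 μg/kg in R and P. The gap of 0.96 μg/kg does not depend on how much pain anyone has.

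**The case against.** The strongest reply is that the outcome section governs. The abstract, section 2.5 and Table 1 all say opioid, which includes oxycodone; only a narrative recap in the Discussion says sufentanil. The article is also condensed, and event-counting rules and equivalence tables are commonly left to the full protocol, case report form or analysis plan. Finally, the trial compares whole strategies and openly declares their fundamental differences, so unequal background opioid is part of what is being tested.

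Much of this stands. The sufentanil wording is a contradiction to be reconciled, not the operative definition, and a missing conversion table alone would not be a finding. What does not fall away is the rescue definition. The article itself labels the bolus as rescue in two arms and then compares rescue requests across three. That is a conflict in what is stated, not an omitted detail.

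Three stronger readings are tempting, and the documents do not support them:
- A reader might infer that every button press is a counted request and that the bias therefore favours L. Section 2.8 implies such counting but does not state it, and if boluses are excluded the bias runs the other way.
- A reader might infer that L's sufentanil total is zero. Only the postoperative part is; the Discussion's total covers surgery as well, and every arm receives 0.5 μg/kg at induction.
- A reader might set 4 requests an hour against roughly 10 a day. The reservoir cannot sustain 4 an hour for a day, and the 10 is a sum of dose limits, not a cap on requests.

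**Conclusion.** The point holds as a definitional fault in secondary endpoints. For rescue, L and the pump arms are not measured on one scale, and the direction of bias depends on a counting choice that the article leaves open. In an open-label trial that choice should be fixed before data are seen. For opioid use, sections of the same article name different quantities. Under the Discussion's wording, L's postoperative part is fixed at 0 against at least 0.96 μg/kg by 24 h in R and P, with L's oxycodone uncounted.

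This rests on the pump running as specified, on L receiving no opioid after surgery other than protocol rescue, and, for the bolus limits only, on a single pump fill. The primary QoR-15 outcome is defined independently of these counts and is unaffected. The plan should be amended on this point, but it does not undermine the main comparison.

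**What to change.** Change definitions only; no dose, schedule or rescue rule needs to change.

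1. Define the rescue endpoints identically in all arms as the time to the first, and the number of, non-pump rescue doses (acetaminophen or oxycodone).
2. Report PCIA boluses separately for R and P.
3. State that the remaining bias runs against L, because R and P have a bolus step before any counted event.
4. Define opioid consumption as all opioids, pump sufentanil (background and bolus) plus oxycodone, on one prespecified equivalence scale, with the intraoperative part kept as a separate component as section 2.5 already implies.
5. Align the Discussion with section 2.5.
6. Note that the background-infusion part of the difference between L and the pump arms is set by design, so that it is not read as an effect of the block on need.

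The cost is endpoint wording and a conversion table. The downside for the sponsor is a less favourable comparison for L: its oxycodone is counted, and R and P keep the advantage of the bolus step. Item 1 does not remove all asymmetry, but it makes the counted event the same in every arm and the direction of the residual bias known.
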